#### Interim analysis

Three interim analyses will be performed at 25%, 50% and 75% recruitment, corresponding to *n* = 22, 44 and 66 participants having completed their 12-week assessments. Each interim analysis will provide an ospportunity to evaluate whether the trial can be concluded at an earlier stage, rather than progressing until the target sample has been fully recruited. The interim analysis will evaluate the level of efficacy achieved, conditional on a linear trajectory of change in PANSS positive scores and an end-of-trial Cohen's *d* effect size of 0.48. The upper (early efficacy) and lower (early futility) bounds and their corresponding mean difference at interim analysis are summarised in Table 2. Conditional power at each interim analysis will be evaluated using bootstrap resampling (*n* = 10 000). Dependent on conditional power at interim analyses, we will consider randomisation reallocation to address the level of imbalance to achieve the desired effect size. The interim analysis will also provide an opportunity to reallocate the proportion of participants allocated to placebo and CBD if the study is found to be underpowered. Results of each interim analysis will be non-binding, with results of interim analyses provided to the Data Safety Monitoring Board (DSMB) for further evaluation.

**Table 2 tab02:** Summary interim analysis upper and lower bounds

	25% (*n* = 22)	50% (*n* = 44)	75% (*n* = 66)	100% (*n* = 88)
Futility boundary conditional power, 1 − *β_c_*	1 − *β_c_* = 0.99	1 − *β_c_* = 0.93	1 − *β_c_* = 0.86	1 − *β_c_* = 0.80
*δ* at futility boundary	*δ* = −4.74	*δ* = 3.53	*δ* = 6.10	*δ* = 7.76
Efficacy boundary (one-sided)	*P* < 0.0089	*P* < 0.0090	*P* < 0.0092	*P* < 0.0094
*δ* at efficacy boundary	*δ* = 15.64	*δ* = 11.06	*δ* = 8.99	*δ* = 7.76

*β_c_* = probability of type II error at differing time points; *δ,* mean difference achieved at interim analysis.

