### Statistical analysis

#### Sample size

A power analysis was conducted based on the mean difference in positive PANSS score between treatment arms at the primary analysis endpoint (12 weeks post-baseline assessment). A mean difference in positive PANSS score of 1.30 at 8 weeks^17^ (extrapolated to a conservative difference of −1.8 at 12 weeks, assuming a logarithmic trend over a linear trend), standard deviation difference of 3.739 (Cohen's *d* effect size of 0.48), correlation between assessment timepoints of 0.6, *α* = 0.025 (one-sided), and 1 − *β* = 0.8, with repeated measures (four assessment timepoints) and analysis of variance (ANOVA) as the planned analysis with pairwise contrast, yielded a requirement of 70 participants. Allowing for 20% dropout and rounding up to the nearest multiple of treatment arms (*n* = 2) suggests that a minimum sample of 88 participants is required overall.

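### The interim looks are triggered by 22, 44 and 66 week-12 completers but labelled as quarters of 88 recruits; with about 70 completers expected, the 75% look falls at about 94% of the data

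*Protocol article*

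**What the plan says.** The protocol's Sample size section states that the power calculation, at α of "0.025 (one-sided)", "yielded a requirement of 70 participants". It continues: "Allowing for 20% dropout and rounding up to the nearest multiple of treatment arms" leads to the conclusion that "a minimum sample of 88 participants is required overall". So 88 counts people recruited, and about 70 is the number expected to contribute a week-12 assessment.

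The Interim analysis section says: "Three interim analyses will be performed at 25%, 50% and 75% recruitment". It equates these with "22, 44 and 66 participants having completed their 12-week assessments". Table 2 uses the same scale, with columns at 25% (n = 22), 50% (n = 44), 75% (n = 66) and 100% (n = 88).

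The looks have two stated purposes. One is to "evaluate whether the trial can be concluded at an earlier stage, rather than progressing until the target sample has been fully recruited". The other is to allow the allocation between placebo and CBD to be changed if the study proves underpowered.

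**The concern.** The figures 22, 44 and 66 are quarters of the 88 to be recruited, yet they are defined as counts of people who have completed week 12. The two scales agree only if nobody drops out, and the Sample size section assumes that 20% will. Completers also lag recruitment by 12 weeks, so a percentage of recruitment and a count of completers are different triggers even without dropout.

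If the stated counts are followed, every look comes later than its label. The third is the serious one, because it arrives when nearly everyone has been recruited and there is little left to stop or reallocate. At stake are the usefulness of that look, the information fractions behind Table 2, and whether the monitoring board has a single clear rule for when to look.

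**Working it through.** **Inputs.** From Sample size: 70 required, 20% dropout, 88 recruited, one-sided α 0.025. From Interim analysis and Table 2: looks at 22, 44 and 66 completers, final n = 88, one-sided efficacy limits P < 0.0089, 0.0090, 0.0092 and 0.0094, and efficacy δ of 15.64, 11.06, 8.99 and 7.76.

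**1. Reproduce the plan's own figure.** 70 / (1 − 0.20) = 87.5, rounded up to 88. This matches. In reverse, 88 × 0.80 = 70.4 expected completers.

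**2. Where the looks fall, read literally.**

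| Completers at look | Label | Share of 70 | Recruits past week 12 needed (n / 0.8) |
|---|---|---|---|
| 22 | 25% | 31.4% | 27.5 |
| 44 | 50% | 62.9% | 55 |
| 66 | 75% | 94.3% | 82.5 |

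With 70.4 as denominator the shares are 31.3%, 62.5% and 93.8%.

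**3. What is left to recruit at the third look.** At most 88 − 82.5 = 5.5 participants, before allowing for those who join during the 12-week follow-up. The recruitment rate is not stated. As an assumption, 0.25 per week adds 3 during the lag (85.5 of 88 enrolled). At 5.5 / 12 ≈ 0.46 per week or faster, recruitment has finished before the look.

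**4. Sensitivity to dropout.** Position of the 66-completer look, 66 / [88 × (1 − dropout)]:

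| Dropout | 0% | 10% | 15% | 20% | 25% |
|---|---|---|---|---|---|
| Share of final completers | 75% | 83% | 88% | 94% | 100% |

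Above 25% dropout there are fewer than 66 completers in the whole trial and the look never happens.

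**5. Which scale Table 2 was built on.** Treating the test statistics as multivariate normal with correlation √(t_i / t_j), the four P limits correspond to z = 2.370, 2.366, 2.357 and 2.349.
- At fractions 0.25 / 0.50 / 0.75 / 1: overall one-sided α = 0.0250, the planned figure.
- At fractions 0.314 / 0.629 / 0.943 / 1: overall α = 0.0227 (0.0228 with 70.4 as denominator; a simulation gave 0.0229).

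The limits were therefore calibrated to quarters of 88. On the completer scale they are slightly conservative.

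**6. Power.** As an assumption, take a drift of 2.80 (1.96 + 0.84, the single-look value for 80% power). Cumulative power after look 3 and at the end is 0.574 and 0.722 with equal quarters, and 0.681 and 0.724 at the literal fractions. The total does not change; the later looks move some of it forward.

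**7. The efficacy δ row.** If δ depends only on the look's own n and P limit, δ × √n / z should be constant. It is 30.96, 31.01, 30.98 and 30.98 for n = 22, 44, 66 and 88. The interim efficacy δ values thus suit their stated n whatever the final n is. The final column does not: with 70 in place of 88, the same scaling gives 7.76 × √(88/70) = 8.70. This check uses only how δ scales with n, not its unit.

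**8. Futility row.** Conditional power depends on the information still to come. After look 3, Table 2 implies 88 − 66 = 22 further completers; the Sample size section implies 70 − 66 = 4. The row is therefore probably affected, but the article does not give enough to recompute it.

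**The case against.** The best defence is that 22, 44 and 66 are meant as recruited participants who have reached week 12, dropouts included. The analysis population supports this: the Data analysis section analyses all participants by mixed model with multiple imputation, so the final n is 88 randomised, as Table 2 shows. On that reading the expected completers are 22, 44 and 66 × 0.8 = 17.6, 35.2 and 52.8, exactly 25%, 50% and 75% of 70.4, and only a loose phrase needs correcting. This stands as a plausible intention. It does not fit the stated trigger, which refers to participants who have completed the assessments, and the choice moves the third look from 66 completers to about 53. Imputation does not rescue the literal trigger either: dropouts accrue in proportion, so 82.5 of 88 randomised participants, still 94%, have passed week 12 by then.

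It is also fair that 20% is a planning allowance, that the accrual rate is unknown, and that the first two looks (27.5 and 55 recruits) can still save recruitment, subject to the lag.

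Three stronger inferences are tempting and are not supported:
- That type I error is inflated. It falls from 0.025 to about 0.0227 to 0.0229.
- That power is lost because the final analysis adds only 4.3 points (0.724 − 0.681) against 14.8 (0.722 − 0.574) with equal spacing. Total power is the same.
- That all of Table 2's δ values are wrong. The interim efficacy δ values are right for their stated n.

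Finally, boundary mechanics often belong in an analysis plan or board charter. Here, though, the protocol itself fixes the counts, percentages and limits, and they disagree. This is a contradiction, not an omission.

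**Conclusion.** The point holds as an inconsistency in the timing of the looks. On the protocol's own 70, 20% and 88, and reading the trigger as written, the looks fall at about 31%, 63% and 94% of the final data. The third look then has almost no scope for either stated purpose: at most 5 or 6 of 88 participants remain to be recruited, possibly none. The information fractions and the n = 88 column of Table 2 do not match the expected data, and the futility row probably does not.

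The harm is to the usefulness and clarity of the monitoring, not to the validity of the final test. The size depends on the 20% dropout (83% at 10% dropout, 100% at 25%) and on the literal reading of the trigger. It should be corrected before the first look, but it does not undermine the trial.

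**What to change.** State one trigger on one scale. Either of these works:

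1. **Randomised participants who have reached the week-12 time point, whether or not they completed:** 22, 44 and 66 of 88. This keeps the 25/50/75% labels and Table 2's P limits, and gives about 18, 35 and 53 completers.
2. **Completers out of the planned 70:** 18, 35 and 53 (25/50/75% of 70 = 17.5, 35 and 52.5), without the equation to percent recruitment.

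Under either option, set the efficacy and futility bounds at the information fraction actually observed, using an alpha-spending function, so that a dropout rate other than 20% does not matter. Recompute the δ and conditional-power rows of Table 2 for the data expected at each look.

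The cost is wording in the protocol and the monitoring board's charter, plus recalculated bounds. No additional participants or assessments are needed. The downside is that each look has fewer completers than the protocol now states (about 18, 35 and 53 instead of 22, 44 and 66), so the mean difference needed to cross at each look is somewhat larger.

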**Method:**

This is a 12-week randomised, placebo-controlled, double-blind, parallel-group trial (registration number: ACTRN12622001112752). We will recruit 88 individuals with clozapine-resistant schizophrenia, randomised (1:1) to 1000 mg daily CBD versus placebo. Eligible individuals will be aged between 18 and 64 years, fulfil DSM-IV criteria for schizophrenia or schizoaffective disorder, have a total PANSS (Positive and Negative Syndrome Scale) score ≥60, have received oral clozapine for at least 18 weeks and have a clozapine level of >350 ng/mL. Interim analyses will be conducted at 25, 50 and 75% recruitment; these will also provide an opportunity to reallocate participants dependent on conditional power. The primary endpoint will be the difference in PANSS positive scores at the end of week 12. Secondary endpoints include depression, anxiety, sleep, quality of life, alcohol consumption, change in weight and metabolic syndrome components, and neurocognitive measures, as well as safety and tolerability.

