### Allocation concealment and randomisation

Participants will be randomised using a chronological process and only after written consent has been provided and baseline assessments have been completed. Participants will be randomised to either the intervention or control group in a 1:1 ratio using a computer-generated randomisation table with block randomisation. They will be allocated a unique identification number, which will be linked to a specific number based on the site they have been recruited from. If a participant withdraws from the study, their identification number will not be re-used, nor will they be allowed to re-enter the study.

Participants, clinical trial staff, investigators and treating clinicians will be blinded to the intervention. An independent biostatistician will generate the randomisation list, which will be provided to the manufacturer and a study site pharmacist. The pharmacist will hold the closed randomisation list and will be the only one who is able to unblind participants. In the case of an emergency, where it is critical that medical staff know whether a participant is on CBD or placebo, participants will be provided with contact information for unblinding (i.e. a 24-h number).

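### With 88 participants and one common SD, changing the CBD:placebo ratio cannot remedy low power at an interim and modestly reduces it

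*Protocol article*

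**What the plan says.** Three statements offer a change of allocation as an interim action.

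- Abstract, Method, on the interim analyses: "these will also provide an opportunity to reallocate participants dependent on conditional power".
- Interim analysis, depending on conditional power: "we will consider randomisation reallocation to address the level of imbalance to achieve the desired effect size".
- Interim analysis, next sentence, where the trigger is low power and imbalance is not mentioned: the look is a chance to "reallocate the proportion of participants allocated to placebo and CBD if the study is found to be underpowered".

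The rest of the design is fixed elsewhere.

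- Allocation concealment and randomisation: participants are "randomised to either the intervention or control group in a 1:1 ratio", in blocks.
- Design and setting, Sample size and the last column of Table 2: the total is 88. Sample size calls this a minimum, but no rule for increasing it is described.
- Sample size: one SD serves both arms ("standard deviation difference of 3.739").
- Data analysis: the fixed effects are arm, visit, site and arm by visit.

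No alternative ratio and no trigger value for reallocation are given.

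**The concern.** The trigger is too little power and the remedy is a different ratio. With two arms, a common SD and a fixed total, equal allocation already extracts the most information, so the remedy points the wrong way whichever arm is enlarged. A board that acted on it would spend power when power is already short.

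There is a second cost. If the ratio changes part-way, later recruits form a larger share of one arm than of the other. Any shift over calendar time in patients, raters or background care then enters the pooled treatment estimate, unless arms are compared within stages.

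**Working it through.** **Inputs.** From Sample size: one-sided α = 0.025, power 0.80, d = 0.48 (the difference is "extrapolated to a conservative difference of −1.8 at 12 weeks"; 1.8/3.739 = 0.481), correlation 0.6 over four assessments, 70 evaluable, 20% dropout, 88 in total. From Interim analysis: looks at 25%, 50% and 75%. **Assumed**, because the article gives none: new ratios of 2:1 and 3:1, a 1-point drift, and a switch that applies to everyone after the look.

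**The plan's own figure.** The article does not print its formula. One that reproduces its result takes week 12 given the other three assessments:

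- variance factor = 1 − 3(0.6²)/(1 + 2 × 0.6) = 0.509
- n per arm = 2(1.960 + 0.842)² × 0.509/0.48² ≈ 34.7, so 35 per arm and 70 in all
- 70/0.8 = 87.5, so 88

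The direction of what follows does not depend on this match, because the variance factor cancels from the comparison of ratios.

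**Power after a switch.** Let f be the fraction recruited before the switch and k:1 the new CBD:placebo ratio.

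- Final CBD share: a = f/2 + (1 − f)k/(1 + k)
- Information relative to 1:1: R = 4a(1 − a)
- Power = Φ(2.80√R − 1.96), calibrated to 80.0% at R = 1

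| Switch | a | R | Power |
|---|---|---|---|
| none | 0.500 | 1.000 | 80.0% |
| 2:1 after n = 22 | 0.625 | 0.938 | 77.4% |
| 2:1 after n = 44 | 0.583 | 0.972 | 78.9% |
| 2:1 after n = 66 | 0.542 | 0.993 | 79.7% |
| 3:1 after n = 22 | 0.6875 | 0.859 | 73.8% |
| 3:1 after n = 44 | 0.625 | 0.938 | 77.4% |
| 3:1 after n = 66 | 0.5625 | 0.984 | 79.4% |

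A shift towards placebo gives the same figures, since R is symmetric in a.

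**Conditional power.** This is the quantity that triggers the rule. Assume an interim estimate of d = 0.20 at the halfway look and a true d = 0.48 afterwards. Conditional power is then 51.4% if 1:1 continues, 45.5% at 2:1 and 37.3% at 3:1. With d = 0.20 afterwards it is 13.1%, 11.4% and 9.2%. It falls in both cases.

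**Time trend.** With 2:1 after n = 44:

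- share of the CBD arm from the second stage: (0.5 × 2/3)/0.583 = 0.571
- share of the placebo arm from the second stage: (0.5 × 1/3)/0.417 = 0.400
- difference: 0.171

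So a 1-point shift in PANSS positive level between stages moves the unstratified estimate by 0.17 points, and 0.17/1.8 is about 9.5% of the planned effect. Stratifying by stage removes this but costs information: R = 0.5 × 1 + 0.5 × 8/9 = 0.944, giving 77.7% power.

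**Restoring balance.** If uneven dropout left 40 and 30 completers, R = 4 × 40 × 30/70² = 0.980 and power is 79.2%. With 42 and 28 it is 78.4%. Returning to 35 and 35 would recover 0.8 or 1.6 percentage points.

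**The case against.** **Imbalance may mean uneven completers.** Blocking balances those randomised, whereas the looks count those who completed week 12, and 20% dropout is allowed for. On that reading the first reallocation sentence aims to return to 1:1, and the argument above supports it. This stands as a reading of that sentence. It does not cover the next one, which makes low power the trigger by itself, and the recoverable power is too small to rescue an underpowered trial.

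**Equal SDs are a condition.** If the SDs differed by an assumed factor of 1.5 or 2, the best unequal split would give 81.5% or 84.0% against 80.0% at 1:1. So it cannot be said that unequal allocation never raises power. But the article plans with one SD and offers no unequal-variance rationale.

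**The losses are small and hypothetical.** The article names no ratio, says only that reallocation will be considered, and makes interim results non-binding. Participants enrolled while the interim cohort completes 12 weeks are already randomised 1:1, so fewer remain to be shifted than the table assumes. All of this stands. It limits the size of the loss but does not turn it into a gain.

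**The bias needs real drift.** A stage term in an analysis plan not shown here would remove it, so its absence from the article is not itself a fault.

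A reader might also infer that the boundaries in Table 2 presuppose equal allocation, or that sites would see a ratio change and guess the interim result. The documents support neither. Table 2 states no allocation assumption. Trial staff, investigators and clinicians are blinded, the list goes to the manufacturer and a pharmacist, and interim results go to the monitoring board.

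**Conclusion.** The point holds in a limited form. With 88 participants and equal SDs, changing the CBD:placebo ratio cannot remedy low power or low conditional power, and it modestly lowers both. From a nominal 80%, the upper-bound loss runs from about 0.3 percentage points (2:1 after n = 66) to about 6 points (3:1 after n = 22) for the assumed ratios. Time-trend bias is a conditional risk: it requires both a drift and an analysis that ignores stage.

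It would be too strong to say that the reallocation wording as a whole defeats its purpose, since one sentence may mean restoring balance. The error lies in tying a new ratio to an underpowered trial. No separate analysis plan could make that work under the article's own assumptions. The change should be made, though the harm is modest.

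**What to change.** In the abstract's Method paragraph and in Interim analysis, delete the option to change the ratio in response to low power or low conditional power, and state that allocation stays 1:1 throughout.

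If imbalance means uneven completer numbers, define it so, limit any reallocation to restoring 1:1, and specify an analysis stratified by stage. Little power is at stake: a stratified analysis adds information across stages, and each stage is most informative when its own arms are equal.

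The cost is wording only. Under the stated assumptions, no option that could raise power is lost. If protection against low power is wanted, it has to come from more participants. For example, at an assumed true d of 0.40, 70 × (0.48/0.40)² = 100.8, so about 102 evaluable and, at 102/0.8 = 127.5, about 128 recruited. That would be a separate adaptation needing its own type I error control.

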#### Participant safety

To assess the preliminary safety and tolerability of 1000 mg daily CBD for 12 weeks in people with clozapine-resistant schizophrenia (secondary objective), we will assess:
the dropout rate between intervention and control groups;the numbers of adverse events reported in the intervention and control groups;liver function test results at baseline and weeks 6 and 12;scores from a structured qualitative interview with participants about their experience with the trial investigational product using the SAFTEE-SI.

All participants will be currently active cases across Queensland Hospital and Health Services. The research team will communicate with clinicians to guarantee that all participants have undergone a regular biannual physical health assessment as part of their standard care. The investigator and clinical trial staff will oversee any adverse events reported during the study. Any adverse events reported between participant consent and final follow-up will be recorded using designated case report forms.

#### Patient withdrawal

All participants have the right to withdraw their consent at any time without prejudice or effect on their ongoing care. This will be clearly discussed during the consent process. If a participant decides to withdraw consent, the trial team will complete a revocation of informed consent form.

#### Reimbursement

Participants will be reimbursed for out-of-pocket expenses, inconvenience and time involved in the trial through the provision of prepaid gift cards. We will provide an AU$20 gift card at the baseline visit and at each fortnightly visit thereafter (total reimbursement AU$140). If the study is terminated by the research team before completion, or a participant withdraws or is withdrawn from the study before completion, a *pro rata* payment will be made at the discretion of the investigator.

## Discussion

Schizophrenia remains one of the most complex and poorly understood psychiatric disorders. This trial seeks to generate new knowledge to support people with schizophrenia by determining the efficacy of add-on 1000 mg daily CBD for treatment of clozapine-resistant schizophrenia. Existing evidence suggests that CBD is well tolerated in this population with minimal side-effects.^42,43^

This trial has some limitations. First, there is no assurance that the study's findings will be generalisable to all individuals with clozapine-resistant schizophrenia. Although the proposed study is sufficiently powered to detect statistically significant differences between groups, the sample size (*n* = 88) is still small. Moreover, as the study sample is required to fulfil eligibility criteria such as abstinence from substances including amphetamine and cannabis, it may not be entirely representative of the real-world population.

This protocol provides a detailed account of the objectives, design, procedures and analytical approach of this trial. We anticipate that the results of the trial will show significant improvements in participants’ PANSS positive scores and will therefore inform clinical guidance on the maintenance treatment of clozapine-resistant schizophrenia. Moreover, we believe that this trial has the potential to minimise symptom severity and optimise quality of life for individuals with clozapine-resistant schizophrenia.

